### Support as usually employed

Families will typically be offered a post-diagnosis follow-up appointment with the diagnosing paediatrician. Parents of children whose symptoms are not severe may be directed to local authority parenting classes. Classes such as ‘Timeout for Autism’ (Cornwall and the Isles of Scilly) and ‘Understanding Autism’ (Plymouth) focus on the features of ASD, instructional parenting techniques and issues associated with education. Psychoeducation may also be offered, with families being directed to relevant resources, for example, The National Autism Society, Gateway ASD and the NHS Child and Adolescent Mental Health Services. For families where a member is experiencing depression or anxiety, treatment varies and is not linked to autism-related care. Initial referral is often through the GP. Patients may receive cognitive behavioural therapy as part of the improved access for psychological therapies service. They may also receive medication and in extreme cases a period of inpatient hospital treatment.

### Proposed sample size

In this feasibility trial no formal statistical testing of between-group differences is planned. Sample size has been selected heuristically with the goal of i) demonstrating that participants can be recruited at a rate sufficient to run a full-scale evaluation of SAFE at a later date; ii) demonstrating that it is possible to train therapists and deliver SAFE to patients within the study treatment settings and iii) demonstrate that the data collection procedures are effective, and that the data collection is acceptable to the 36 families, and not overly burdensome.

### Data analysis

Completed paper case report forms will be checked and signed by research staff before being sent to the Peninsula Clinical Trials Unit (CTU). Original case report form pages will be posted to the CTU at agreed time points for double-data entry on to a password-protected database, with copies retained at the study site. Forms will be tracked using a web-based trial management system. Data will be analysed and presented as is appropriate for a feasibility study, in particular concentrating on descriptive analyses and undertaking no formal comparisons between groups. Reporting will follow the principles of the CONSORT statement using the checklist and flow chart as recommended in the CONSORT extension for randomised pilot and feasibility.^63^ The flow chart will provide details about the number of families approached, number eligible, number consenting, number randomised, number receiving allocated intervention and number assessed for outcome data at each time point. As appropriate, details will be given for individual members of the family, for example, how many family members there are and how many completed each questionnaire. Wherever possible, detailed reasons will be given for exclusions, loss to follow-up, non-completion of outcome measures, etc.

Numbers will also be provided by centre and group, to inform the logistics of recruiting nine families prior to randomisation and following them up after randomisation. For those randomised to the SAFE intervention, adherence will be reported according to the number of group sessions attended and participation of individual family members at each of the therapy sessions. Completeness of data will be reported for each outcome measure at each relevant time point. Again this will be reported for individual family members as appropriate.

For each outcome measure, the relevant scores will be calculated and presented descriptively by trial arm. Where available, published guidelines will be used to process, score and summarise the measures including, for example, the use of imputation in the event of missing items on a questionnaire. Summary measures will be calculated as appropriate, for example, means and SD, medians and ranges, numbers and percentages in categories. These measures will be presented both for baseline and for the final follow-up. The only analysis contrasting the two groups will be an interval estimate in the form of a 95% CI for the primary outcome, so that the plausibility for the effect size used in the sample size calculation for the full trial can be assessed. For this purpose, the baseline values will be used in an analysis of covariance, with acknowledgement that no effects are included for group or therapist.

Focus group interviews will be audio recorded and transcribed verbatim. Consequent qualitative data will be managed using proprietary computer-assisted qualitative data analysis software, for example, NVivo 10, and analysed thematically.^64 65^ Rigour of analysis will include ‘respondent validation’, whereby participants are provided with a summary of their transcript and analysis so that they can assess whether the interpretations being made about the data, accurately represent them. In addition, a second qualitative researcher will conduct an independent analysis of a subset of half of the focus group transcripts. Researchers will then meet to discuss and agree the findings, which will then be presented to the Family Consultation Group for discussion.

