**Methods and analysis:**

Families of children with autism aged 3–16 years will be invited to participate. Consenting participants will be randomised 2:1 to either SAFE+support as usual or support as usual alone. The proposed primary outcome measure for the main trial will be the Systemic CORE 15. Participants will also complete proposed secondary outcome measures, indexing changes in child behaviour, child-parent attachment, anxiety and depression. Generic health economic outcome measures (EuroQol 5 dimensions and Child Health Utility 9 Dimensions) will also provide data on the feasibility of cost-effectiveness analysis. Questionnaires will be completed at baseline and 32 weeks post-allocation. Data on ability to identify, recruit, randomise, retain and collect data from families, acceptability of outcome measures, adherence of therapists and families to the intervention, appropriateness of resource use questionnaires and effectiveness of training will be collected for feasibility analysis. Qualitative data will also explore acceptability of SAFE and reasons for declining and withdrawing from the study.

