### Study design

This is a randomised controlled, multicentred feasibility study including children with autism and their families (See the study schema shown in figure 1.) A total of 36 families will be recruited in four cohorts and each cohort will be randomised in a 2:1 ratio to receive support as usually employed (SUE) plus a programme of SAFE therapy, or SUE alone, for a period of 16 weeks. Advantages of 2:1 allocation include:

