### The intervention

SAFE is a manualised intensive programme of systemic family therapy designed to treat maladaptive autistic symptoms and mental health-related difficulties encountered by families of children with autism. SAFE provides an array of therapeutic activities based on attachment theory, established systemic practice and the known visual processing preferences of people with autism.^59–61^ SAFE is best seen as a toolkit with a variety of activities which can be applied to family therapy flexibly. For example, a very young child will engage with activities in a different way to teenagers. Activities include visual tasks, drawing, modelling, role-play and tracking circular patterns. Sessions are led by family need and the therapists and family work collaboratively, often in a playful way, using family resources, therapist expertise and the tools that SAFE provides. SAFE draws heavily from well-documented active and playful approaches in family therapy practice and literature.^62^

Each therapy session will include two therapists with a minimum of intermediate family therapy level of qualification and 4 days training in SAFE principles. Prior to the therapy sessions parents allocated to SAFE will complete an adapted version of the parent development interview,^60^ which will provide therapists with background information on family experience. The reflective functioning questions of this interview will also be revisited as an opportunity to discuss change at the 24-week follow-up. Between weeks 1 and 16, families allocated to the SAFE intervention will attend five 3-hour SAFE therapy sessions. Sessions 1 and 5 are multifamily sessions and will take place in a community setting. Sessions 2, 3 and 4 are for individual families and will take place in a community venue or the family home. The therapists will facilitate sessions which will be video recorded, as is usual practice for therapy sessions. The videotapes will be used by the therapists in supervision sessions and preparation for subsequent sessions.

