Following completion of the therapy programme, families will attend a group follow-up session at 24 weeks post-allocation. Families will discuss any changes they have encountered focusing on their ability to be reflective about challenges faced and solutions tried. Trained support workers from local voluntary groups will attend this follow-up session and will be invited to give the families information about continued support for families of children with autism through existing networks.

Each session will include the following assessments for families to complete:Client Satisfaction Questionnaire 8.The Helpful Aspects of Therapy Questionnaire.A Between-Session Activity (BSA) homework activity. Families will be encouraged to complete a pro forma with key elements of the intervention as prompts for families to track strengths and difficulties in response to SAFE ideas. Completion of the BSA will be recorded.

At the end of each session, the therapists will also complete a training checklist and questionnaire to monitor protocol adherence.

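### The only between-arm interval ignores randomisation within cohorts and multifamily delivery of SAFE; the effect is modest and cheap to correct

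*Protocol article*

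**What the plan says.** - **Randomisation.** Study design in the protocol article: "A total of 36 families will be recruited in four cohorts and each cohort will be randomised in a 2:1 ratio". Data analysis gives the cohort size: "Numbers will also be provided by centre and group, to inform the logistics of recruiting nine families prior to randomisation".
- **Delivery.** The intervention section describes five therapy sessions, each run by two therapists: "Sessions 1 and 5 are multifamily sessions and will take place in a community setting". Sessions 2 to 4 are for single families. After the programme, "families will attend a group follow-up session at 24 weeks post-allocation". All of this comes before the 32-week outcome and happens only in the SAFE arm.
- **Analysis.** Data analysis allows one contrast between arms, a 95% confidence interval for the primary outcome. Its purpose is to show whether the effect size assumed for the full trial's sample size is plausible. The model is an ANCOVA using baseline values, "with acknowledgement that no effects are included for group or therapist".
- **Context.** Proposed sample size states that the number of families was chosen heuristically and that no formal test between arms is planned.

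**The concern.** The interval treats the 36 families as independent and as randomised without restriction. Neither is true.

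Allocation is balanced within each cohort, so differences between cohorts cancel out of the arm contrast. If cohort is not in the model, those differences stay in the residual and the interval is wider than it needs to be. Such differences are plausible: the article links recruitment before randomisation to an area, and usual support differs between Cornwall and Plymouth.

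SAFE families who attend multifamily sessions together may also have correlated outcomes, while control families have no matching structure. Ignoring this makes the interval too narrow.

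The documents do not settle which effect is larger, so a reader cannot tell the direction of the net error. At stake is the accuracy of the limits of the trial's one comparative estimate, which is meant to feed into planning the full trial.

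**Working it through.** **Design arithmetic.** No power calculation exists to reproduce. The structure is internally consistent: 36/4 = 9 families per cohort, as stated; 2:1 within nine gives 6 SAFE and 3 control; overall 24 and 12.

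**Assumptions.** The documents give no ICC, SD or baseline correlation. The figures below assume a baseline-outcome correlation r = 0.5, one analysed score per family, complete follow-up, and the six SAFE families of a cohort forming one therapy group. ICCs are varied.

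**Interval as planned, with no clustering.** In outcome SD units:
- SE = √(1 − r²) × √(1/24 + 1/12) = 0.866 × √0.125 = 0.306.
- Residual df = 36 − 3 = 33, t = 2.035, half-width = 0.62 (0.72 if r = 0).

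**Clustering in the SAFE arm only.** The design effect is 1 + (6 − 1) × ICC, applied to the 24 SAFE families. The variance factor is (1 + 5 × ICC)/24 + 1/12, against 0.125 without clustering. Coverage of the planned interval is by simulation (15,000 runs).

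| ICC | Design effect | Variance factor | SE ratio | Effective SAFE n | Coverage |
|---|---|---|---|---|---|
| 0.01 | 1.05 | 0.1271 | 1.008 | 22.9 | not simulated |
| 0.05 | 1.25 | 0.1354 | 1.041 | 19.2 | 93.8% |
| 0.10 | 1.50 | 0.1458 | 1.080 | 16.0 | 92.9% |
| 0.20 | 2.00 | 0.1667 | 1.155 | 12.0 | 91.0% |

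**Shared cohort effect only.** The planned interval covers 95.8%, 96.0% and 96.6% at cohort ICCs of 0.05, 0.10 and 0.20. Adding cohort as a fixed effect returns coverage to about 95% and narrows the interval by about 2%, 4% and 8%. At 0.10 the mean full width falls from 1.243 to 1.198 SD.

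**Both present, each at ICC 0.10.** Planned coverage is about 93.9%. Adding cohort alone lowers it to about 92.4%, because the interval narrows while the SAFE-arm clustering remains. Multiplying that SE by 1.080 brings coverage to about 94.4%. A separate simulation gave 93.6% and 92.1% for the first two figures, the same pattern within simulation error.

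**The case against.** The case for leaving the plan alone has real force.

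- **It is disclosed.** The article itself says that the effects are left out, so this is a declared simplification and neither a contradiction nor a concealed error. That stands and lowers the weight. But acknowledging the omission does not change the limits, and the article gives no allowance for it.
- **An article need not list every covariate.** True in general. Here, though, the article does describe the model for this interval and says what it leaves out, so the mismatch lies in what is stated.
- **The stakes are low.** There is no test, and no plausibility judgement has been shown to change. At ICC 0.10 the clustering correction adds about 0.05 SD (0.62 × 0.08) to the half-width. That stands.
- **The errors partly cancel, and cohort adjustment alone can make coverage worse.** Correct, and the remedy has to allow for it.
- **Group size and therapist sharing are not stated.** Also correct. The article gives no size for the multifamily sessions and does not say whether therapists serve several families. Three of the five therapy sessions are for single families, so exposure to grouping is partial.

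Two stronger readings are tempting. A reader might infer that having no effect for *group* removes the arm effect, since the arms are called groups two sentences before the quoted clause. The text does not support this: the interval is expressly a contrast of the arms, *group* is paired with therapist, and the same section elsewhere links the word to the nine families. A reader might also infer that the interval's precision is uninterpretable. Coverage of about 91% to 97% across all the scenarios above does not bear that out.

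**Conclusion.** The mismatch is real and minor. The baseline-only ANCOVA reflects neither randomisation within cohorts nor grouped delivery of SAFE. Under the stated assumptions each source alone shifts coverage by roughly one to two percentage points at ICCs of 0.05 to 0.10, in opposite directions; the net direction cannot be determined from the documents. The structure of four cohorts of nine, randomised 2:1, is documented. One therapy group of six per cohort, every ICC, r = 0.5 and complete data are assumptions, so the sizes are illustrative. The point merits correction because the interval has one declared use, judging the effect size for the full trial, and matching it to the design costs little.

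**What to change.** 1. Fit the ANCOVA with arm, baseline and cohort (four levels, fixed).
2. Always report beside it confidence intervals with the SAFE-arm variance inflated by 1 + (m − 1) × ICC for ICC 0.01, 0.05 and 0.10, where m is the actual multifamily group size (6 if each cohort forms one group). With 24 and 12 families, multiply the SE by √{[(1 + (m − 1) × ICC)/24 + 1/12]/0.125}, replacing 24 and 12 by the numbers analysed. Assumed ICCs are used because four therapy groups cannot estimate an ICC usefully.
3. State that the uninflated interval may be too narrow. Do not adopt step 1 without steps 2 and 3.
4. As a wording matter, say whether *group* means the randomisation cohort or the multifamily therapy group.

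**Cost.** Three degrees of freedom (33 to 30; t from 2.035 to 2.042) and sensitivity intervals wider by about 0.8%, 4.1% and 8.0% when m = 6. Nothing changes in recruitment, delivery or data collection.

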### Patient and public involvement

Families of children with autism initiated the development of this project by communicating their complex needs and dissatisfaction with current service provision through the Plymouth Autism Network. This Network was set up by the Chief Investigator in 2011 to bring clinicians, carers, academics and individuals with autism together to share ideas, research findings and experiences. We further explored the challenges facing families of children with autism by conducting in-depth interviews and surveying over 90 families regarding their needs and the treatment they received post-diagnosis. Less than 9% of families agreed that current treatment helped with the problems they face. Our survey revealed a strong need for interventions, which support the whole family.

This pilot data led to the development of a research team within the Welcome Research Hub at Plymouth University, which included a Family Consultation Group. Our Family Consultation Group worked with us to develop and refine the SAFE intervention prior to the current project. These families have also contributed to the creation of a recruitment and treatment plan, which will be manageable for families. They have offered advice about how it is best to communicate with families at the start of the study and as it progresses. In addition, the Family Consultation Group representative is a co-applicant on this study.

Our Family Consultation Group will continue to be essential members of the team and work as an advisory group throughout the feasibility study and beyond. Formal structures are in place to ensure ongoing collaboration with the Family Consultation Group. Specifically, the representative for the Consultation Group is paid as a research assistant on the trial and is a co-applicant. She attends and actively contributes to monthly trial management group (TMG) meetings, all training sessions and fortnightly research team meetings. The representative reports key issues and requests to and from the wider group. Where necessary, additional meetings are held between the Family Consultation Group as a whole and other research staff. In these instances, travel and subsistence costs are available in line with NHS England guidelines on working with our patient and public voice partners.^66^

We see our Family Consultation Group as experts in their own lives and the lives of families with similar challenges. For this reason, we feel our role is to work with them in a supportive manner as collaborators. Their contribution is valuable in the same way as other experts on the team and we aim to facilitate one another. As stated above, the Family Consultation Group have been active in contributing to the research plan. Their input is of particular value in developing recruitment procedures, designing participant information packs and providing information about potential barriers to retention. We have also worked with them to prepare and deliver a training programme for research staff and therapists. With their help we have trained recruited staff to work in a sensitive and informed manner with participants. We also value their input in interpreting and reporting data; in particular commenting on possible ways to overcome challenges for the main randomised controlled trial.

Our families can help by identifying local networks and sharing their experience with new groups. Our Family Consultation Group are proactive campaigners for change and have extensive knowledge of existing bodies such as the National Autistic Society. They can also provide a family-centred perspective on research outcomes. They are, therefore, well-placed to collaborate with us in planning next steps and disseminating findings at local and national levels.

## Ethics and dissemination

### Risks and safety

Families of children with autism are a potentially vulnerable group. The risks associated with participating in this study are however, considered minimal, with no adverse events anticipated in any participant. For those in the intervention group, there is a slight chance that the SAFE family therapy sessions could lead to an initial increase in family disagreements as family members learn how to change the way they solve problems and talk with one another. However, the purpose of the intervention is ultimately to equip families with skills to handle these difficulties by learning how to change the way they solve problems and improve their communication, and the SAFE family therapists will be available to provide support and will be trained to handle any emerging problems. Should any issues arise the SAFE family therapists will have access to two consultant clinical psychologists to provide further support and advice.

During the trial, the children with autism will remain in the care of the Child Development Centre or the ASDAT and will have access to usual care should any unforeseen circumstances arise. Other members of the family will also continue to be able to seek care and advice from the GP or any other specialist services they are concurrently involved with.

### Monitoring adverse events

The research team have mechanisms in place to report serious adverse events (SAE) related to mental health. SAEs related to mental health may be volunteered by the participant or discovered by the therapists, research assistants or other member of the research team during the SAFE family therapy sessions, or as a result of direct reporting (e.g. by telephone) by a family member, independent clinician or other informant. SAEs will be recorded from the time of consent until the date the participant completes the follow-up or withdraws from the study.

If the CI considers that the SAE is not, or is unlikely to be, associated with the trial, the CTU will obtain a second assessment of causality from an independent assessor. Any SAE which in the opinion of either adjudicator is possibly related to the trial will be reported to the Research Ethics Committee (REC) within 15 days of the local research team having become aware of the event. All SAEs will be followed until either stabilised if chronic conditions, or resolved.

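### The SAE capture rule covers only mental-health events while later sentences carry no such limit, so other serious events have no stated route to causality assessment or the ethics committee

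*Protocol article*

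**What the plan says.** The section Monitoring adverse events in the protocol article sets the scope in its first sentence: "The research team have mechanisms in place to report serious adverse events (SAE) related to mental health". The second sentence keeps the same scope for detection: "SAEs related to mental health may be volunteered by the participant or discovered by the therapists, research assistants or other member of the research team", with direct reports from a family member, an independent clinician or another informant as a further route.

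The qualifier then disappears:

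- Recording window: "SAEs will be recorded from the time of consent until the date the participant completes the follow-up or withdraws from the study".
- Second opinion on causality, given by someone independent: "If the CI considers that the SAE is not, or is unlikely to be, associated with the trial, the CTU will obtain a second assessment".
- Ethics reporting, with a 15-day limit that runs from the local team's awareness of the event: "Any SAE which in the opinion of either adjudicator is possibly related to the trial will be reported to the Research Ethics Committee (REC").
- Follow-up: "All SAEs will be followed until either stabilised if chronic conditions, or resolved".

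The section Risks and safety describes the families as potentially vulnerable, rates the risks as minimal and anticipates no adverse events. It names one possible harm, rated as slight: the sessions "could lead to an initial increase in family disagreements". The section on informing potential participants repeats that risk and adds difficult emotions.

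**The concern.** The causality procedure is a good safeguard. The chief investigator judges association, a doubtful or negative judgement is checked independently, and either opinion is enough to trigger an ethics report. It can act only on events that enter the system, and the stated entry condition is the type of event. Type and relatedness are separate questions. If type is settled first, an event that the trial caused but that nobody classes as mental-health related may never be put to the chief investigator.

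The filter also fits the article's own named risk poorly. That risk is family disagreement, in families whose children, according to the abstract and introduction, show challenging behaviour. The serious end of family conflict could include an injury to a child, sibling or parent, and such an injury need not be classed as a mental-health event.

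At stake are the protection of a vulnerable group and the meaning of the SAE count that will inform the main trial. If the scope is unclear, a low count cannot be told apart from narrow capture.

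**Working it through.** The article gives no figure to reproduce here, so the check is mainly a reading of the text.

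**Step 1. Scope by function, Monitoring adverse events.**

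| Function | Limited to mental health? |
|---|---|
| Reporting mechanism | Yes |
| Routes of detection | Yes |
| Recording window | No limit stated |
| Second causality assessment | No limit stated |
| Report to the ethics committee | No limit stated |
| Follow-up | No limit stated |

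**Step 2. The two possible readings.**

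- *The later sentences refer back to the first two.* This is the natural reading, since the first two sentences introduce the events being discussed. A serious event of another type then has no stated route into recording, causality assessment or ethics reporting.
- *The later sentences cover every SAE.* This is the literal reading. All SAEs must then be recorded and followed, but the mechanism and the detection routes are described for only some of them, so the first two sentences are too narrow.

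On either reading the section needs correcting.

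**Step 3. Is there another route elsewhere in the article?**

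- Focus groups explore potential harm (Outcome measures, qualitative component), but only after the 32-week assessments and with voluntary attendance.
- The Resource Use Questionnaire asks about the child's healthcare use, including days in hospital, and is matched to medical records in a subgroup. It is an economic measure and concerns the child only.
- Therapists can call on two consultant clinical psychologists, and usual care continues (Risks and safety). These are support, not reporting.

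None of these is linked to causality assessment or to the ethics committee.

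**Step 4. Workload if every SAE is recorded.** From the article: 36 families, each taking part for about 8 months (Study design). Assumed, because the article does not give them: 3 to 4 participating members per family, and 5% to 10% of people having a serious event per year.

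Expected reports = families × members per family × annual rate × 8/12

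- Low: 36 × 3 = 108 people; 108 × 0.05 × 8/12 = 3.6
- High: 36 × 4 = 144 people; 144 × 0.10 × 8/12 = 9.6

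That is about 4 to 10 reports over the whole study. Under these assumptions it overstates the extra load, because some of these events would be mental-health SAEs that are captured already.

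**The case against.** The strongest reply is that this is a condensed article. Its reference to mechanisms already in place points to procedures held elsewhere, and definitions, forms and responsibility for classification usually sit in the full protocol. The trial is also to be run under ICH GCP. Concentrating on the event type most relevant to a minimal-risk talking therapy is a defensible choice, and a serious injury arising from family conflict might well be reported under a phrase as broad as the one used. Causality assessment is central, through the chief investigator and the CTU, which limits how far the two sites could diverge.

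Part of this stands. The article cannot be faulted for omitting forms and definitions, and the full protocol may be clearer. But the limit is stated twice and then dropped, so this is more than detail left out.

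A reader might also infer stronger claims that the article does not support:

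- *That whoever notices an event decides whether it counts.* The section lists who may volunteer, discover or report an event. It names nobody as classifying it.
- *That the therapy is expected to raise conflict.* Risks and safety calls the chance slight and anticipates no adverse events.
- *That other serious events are never captured.* No sentence excludes them, and the later sentences are unqualified. No stated route is as far as the text goes.
- *That every SAE gets two assessors.* The step in which "the CTU will obtain a second assessment of causality from an independent assessor" applies only when the chief investigator considers the event not, or unlikely to be, associated with the trial.
- *That physical injury is a recognised harm of SAFE.* The article names disagreement and difficult emotions. Injury is an inference.
- *That the harms evidence is biased downwards by a known amount.* Nothing in the article allows that to be quantified.

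**Conclusion.** The point holds as a defect of scope. The mechanism and detection routes are limited to mental-health events, the later functions are not, and on the natural reading a type filter acts before relatedness is judged. No other part of the article supplies a route to causality assessment or the ethics committee.

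The number of events that might be missed cannot be estimated from the article. The conclusion rests on reading the later sentences as referring back to the first two; on the literal reading, what remains is an inconsistency with the same remedy. No planned comparison depends on it, since the trial is descriptive apart from one confidence interval for the primary outcome. The change is still worth making, because it concerns the safety of a vulnerable group and the harms data carried into the main trial, at little cost.

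**What to change.** Use one scope throughout Monitoring adverse events:

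1. Remove the mental-health qualifier from the sentences on the mechanism and the detection routes, so that every SAE in any participating family member, in either arm, is recorded.
2. State that the chief investigator classifies each SAE by type (for example mental health, injury or conflict, other) and by relatedness, with the independent assessor involved where the existing rule calls for it.
3. Leave the expedited rule unchanged: only SAEs that either adjudicator considers possibly related go to the ethics committee within 15 days.

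The cost is a wording change to the section and the SAE form, and at most roughly 4 to 10 extra reports to classify under the stated assumptions, most of them probably unrelated to the trial. No new visits or staff are needed. The change widens what counts but does not make detection more active: events would still come to light by being volunteered, discovered or reported.
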